#### Secondary outcomes

Besides the primary outcomes, the present study distinguishes several secondary outcomes. Information about *school and/or work situation* will be retrieved from the local government system of Rotterdam. This will show whether the participant works or attends school (“yes” or “no”) at T2 and T3. The type and level of education and field of work, as well as self-reported nonregistered work, may be added as descriptive data.

*Quality of life* will be assessed with the Dutch version (developed by Van Nieuwenhuizen and colleagues) [88] of the Manchester Short Assessment of Quality of Life (MANSA) [89]. The MANSA involves the satisfaction of the participant with his situation regarding important domains of life such as his mental health condition, relationships and financial situation. The questionnaire consists of 16 items and has adequate psychometric properties [89].

The Adult Self-report (ASR) will be used to assess *psychopathology* in terms of depressive problems, anxiety, somatic problems, avoidant personality problems, attention deficit/hyperactivity problems and antisocial behavior, consistent with the respective diagnostic categories of the Diagnostic and Statistical Manual of Mental Disorders – 4th edition (DSM-IV) [90]. The questionnaire, consisting of 123 items (three open questions not included), is validated for many different cultures [91].

*Cognitive distortions* will be measured by the “How I Think” questionnaire (HIT, in Dutch: HID [92]), a widely used and validated 54-item questionnaire that is based on a four-category typology of self-serving cognitive distortions, namely *self-centeredness*, *blaming others*, *minimizing/mislabeling* (e.g., antisocial behavior causes no real harm or is acceptable) and *assuming the worst* (e.g., attributing hostile intentions to others) [92–95]. These categories can be related to four types of antisocial behavior: opposition-defiance, physical aggression, lying and stealing. The Dutch version has been developed and validated by Nas and colleagues [92, 95].

*Substance use* will be assessed with the first module of the Measurements in the Addictions for Triage and Evaluation (MATE) [96, 97]. The participants will be asked about the prevalence, frequency and average amount of used nicotine, alcohol, drugs and gambling in the last 30 days. Additionally, we will ask the participants what the onset of substance use is and what, according to them, the principal problematic substance is. The MATE is appropriate for a heterogeneous population [96].

#### Potential moderators: participant characteristics

Questions regarding *demographic characteristics* (e.g., age, ethnicity) will be administered. Additionally, *intellectual functioning* will be measured by the Screener voor intelligentie en licht verstandelijke beperking (SCIL), an instrument for measuring the appearance of a mild intellectual disability, and by a short form of the Wechsler Adult Intelligence Scale – third version (WAIS-III SF). The SCIL is a relatively new instrument, which has been developed and validated by Kaal, Nijman and Moonen [98] and consists of a combination of assignments (i.e., calculating, writing, reading, spelling, understanding a proverb, drawing a clock) and questions about previous education, contact with intellectual disability services, support from family and reading behavior. The SCIL (14 items) has an adequate sensitivity and specificity [98]. The WAIS-III SF estimates more specifically the level of intelligence of the participants. This version, studied by Blyler and colleagues [99], consists of four subtests of the WAIS-III – namely, digit symbol coding, information, block design and arithmetic – and will be administered at T1. Moreover, information about *criminal history* will be gathered with the SRD (frequency and nature of offenses ever committed in life) and official data (age of first offense, history of offenses). Finally, the present state of *treatment motivation* will be assessed with the validated 17-item Motivation for Treatment Questionnaire–Short Form (MTQ-SF, in Dutch: VMB) [61], based on the questionnaire of Van Binsbergen [100]. The theoretical framework underlying this questionnaire is the Transtheoretical Model of Prochaska and DiClemente which describes the different stages of behavioral change regarding motivation [101, 102].

#### Potential moderatos: treatment characteristics

*Group climate* is measured by the Group Climate Instrument (GCI), consisting of 36 items that represent four scales of group climate: Support, Growth, Repression and Atmosphere [103, 104]. The participants are also asked which grade (and why) they will give to the domains of support, learning, atmosphere, honesty and rules regarding their intervention. The questionnaire has been validated for Dutch youth prisons and forensic psychiatric institutions for adults [103].

The *therapeutic relationship* or *working alliance* is measured by the Flemish Work Alliance Inventory (WAI, in Dutch: Werk Alliantie Vragenlijst), developed and validated by Vervaeke and Vertommen [105]. The WAV has three subscales regarding *bonding* (agreement between therapist and client regarding), *tasks* and *goals* based on the theory of Bordin [106]. Both the client and therapist version of the questionnaire consists of 36 items (12 per scale).

We will gather *general program characteristics* (i.e., duration, frequency, type of treatment and treatment completion) via registration systems. Participants will also be asked questions about their attendance and experiences with the intervention (at T1 and T2 when still participating in the intervention).

#### Program integrity of DNK

The two versions (both participant and staff member) of the program integrity questionnaire are based on the DNK protocol and on qualitative semistructured interviews about the program – held by the first and second authors – with staff members, participants and important partners (e.g., the social welfare agency) of DNK. At the end of the DNK trajectory of a participant, both the participant and his coach/mentor will fill out the questionnaire about the process of the participants’ trajectory: the development and attendance during the three phases of the program, the tailoring of the last phase, the individual adjustments of the protocol, the development of motivation, the estimated degree of success of the program and possibilities for the future regarding school/work. Furthermore, the participants will be asked about their experiences and the strengths and weaknesses of the program. Additionally, the staff will complete a general questionnaire twice a year (a total of 4 times) about their experiences with their treatment population, team functioning, collaboration with external parties and possible chokepoints.

#### Cost-effectiveness

Costs in terms of health care utilization (direct costs; part 1) and productivity loss (indirect costs; part 2) will be assessed with an adapted version (consisting of 38 questions) of the Trimbos/iMTA questionnaire for Costs associated with Psychiatric Illness (TiC-P) [107, 108]. Regarding part 1 of the questionnaire, specific services for multi-problem young adults, contact with the police and justice system, probation services, organizations for housing and arrangements for debts have been added to the original questionnaire. Questions about school and social welfare have been added to part 2. Several tools have been appended (e.g., list of frequently used medicines) to make the questions understandable for this specific group. The questionnaire gives insight into the societal costs of the last 3 months before T3.

### Statistical analysis

Primary analyses will be conducted in accordance with the *intention-to-treat principle* (ITT) [75, 109–112]. Additionally, a second analysis will be performed in which only participants who actually started with the intervention are included. By conducting these two analyses, we will be able to measure both the effectiveness of *assigned* treatment and *actual* treatment which could provide valuable information for clinical practice [113].

The outcomes at T3 will be used to determine the main effects of DNK compared to CAU. Missing data at T3 will be imputed according to the multiple imputation approach, for which we will use LISREL 8.8. This approach follows the expectation maximization algorithm (maximum likelihood estimation) [114, 115]. The primary and secondary continuous outcome measures (i.e., self-reported recidivism, self-sufficiency, quality of life, psychopathology, cognitive distortions and substance use) will be analyzed with independent samples *t* tests, using treatment condition (DNK versus CAU) as independent variable and the outcome measures as dependent variables. The effect sizes are computed as Cohen’s *d*, based on adjusted means and standard deviations. The categorical outcome measure *work/school* will be examined with a chi-square test. An odds ratio will be calculated as effect size. To obtain insight into the *time to recidivism* (i.e., recorded delinquency) survival curves will be drafted. To examine the differences in registered recidivism between DNK and CAU, a Cox regression analysis will be conducted. The hazard ratio will be used as effect size.

To gain more insight into the possible differences between DNK and CAU in the development of the primary and secondary treatment outcomes up to and including T3, additional analyses will be conducted by means of mixed-model analyses for the continuous outcome measures (i.e., recidivism, self-sufficiency, quality of life, psychopathology, cognitive distortions and substance use) and Generalized Estimating Equations (GEE) for the categorical outcome measure *work/school*. In these analyses, the outcome data of T0, T2 and T3 will be included. T1 data are excluded from the analyses since T1 is an additional assessment point to measure treatment characteristics and, therefore, not all primary and secondary outcomes are included at T1. In the mixed-model analysis *treatment condition* and *time* (i.e., the assessment point: T0, T2 or T3) will be set as fixed factors, and the participants as a random effect. By analyzing the interaction between treatment condition and time, differences between both groups in development over time can be examined. If the overall interaction is significant, post-hoc analyses will be conducted to investigate at which time point the differences can be found. A similar analysis will be conducted with GEE, using an unstructured correlation matrix to account for within-subject correlations due to repeated measures.

Subsequently, moderator analyses will be carried out by the addition of potential moderators as covariates (in case of continuous variables) or as factor (in case of the categorical variable work/school) to the abovementioned mixed-model and GEE analyses. A three-way interaction between treatment condition, time and moderator will give insight into the influence of a moderator on the development in outcome between DNK and CAU. Post-hoc analyses will be carried out if the model appears to be significant. Moderators regarding registered recidivism will be examined with Cox regression analyses (a two-way interaction between treatment condition and the moderator).

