Multi-problem young adults aged between 18 and 27 years will be recruited after their first interview at the social welfare agency in Rotterdam. After informed consent is obtained, baseline measurement (T0) will take place. After T0, the random assignment (with a ratio between DNK and CAU of 1:1) will be carried out by the first author. The random allocation is determined via an online computer program for randomization (www.random.org). Subsequently, the randomization numbers will be kept in sealed envelopes at the social welfare agency. During the baseline measurement the participant, researcher and youth coach will still be blind to the treatment condition. The first author will inform the youth coach about the outcome of the randomization. Only at the second interview will the young adult be informed by the youth coach about the assignment to the treatment or control condition. During the phase between the first and second interviews, the so-called statutory effort period, no intervention takes place. Only the participants who return for a second interview can be referred to an intervention. Therefore, participants who do not return within the run-in period will be excluded from the analyses. In this way, the statutory effort period is considered as a run-in period [74, 75] to deal with the estimated dropout rate of approximately 40% (p. 9) during this period [71]. Although some researchers have pointed out that a run-in period may influence the generalizability of the results [74, 76], it will improve the internal validity – the primary condition for valid outcomes – of our study [77]. Of the subjects who will be excluded during the run-in period, data will be collected at the follow-up measurements to compare the outcomes of the included and excluded groups and to incorporate this in generalizations from the study [74]. Figure 1 shows the flowchart of this study and Fig. 2 shows the SPIRIT schedule of enrollment, interventions and assessments.

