Despite the strengths of this study, several pitfalls might threaten the quality of our study. A great challenge will be realizing an adequate response rate at baseline and follow-up measurements. As our target group often has an extensive history of youth care and criminal justice services, they may have negative experiences with formal help and are reluctant to make an appeal to these services again [4]. Moreover the participants probably have completed questionnaires on a regular basis within the context of diagnostic tests or examinations. Therefore, they may have become tired of questionnaires or suspicious about their purposes [80]. To keep the nonresponse rate as low as possible, the research team will be well trained, outreaching, attentive, flexible and will give clear information about the content, goals and procedures of the study to the participants. As it could be difficult to trace them for follow-up measurements – because of many changes in telephone numbers, addresses and social network [80] – we will put much effort in maintaining contact with the respondents (e.g., by making contact via calls, Whatsapp, Short Message Service (SMS), e-mail and Facebook; by contacting their families and third parties; and by visiting them at home).

Another possible threat to the value of our study is the risk of nonadherence to interventions (i.e., risk of dropout of *treatment*) due to the combination of multiple problems in the lives of these young adults, the difficult referral path from intake at the social welfare agency to start at the interventions, and the early moment of randomization [79, 80]. Unfortunately, it is not possible to conduct the randomization in a later stage as a consequence of legal requirements. However, the advantage of this situation is that the referrers will be involved in the randomization process [79] and we will fit in with the guidelines of pragmatic trials (i.e., staying close to normal practice and obtaining insight into the whole target group) [67]. To prevent the study from showing a distorted view due to large dropout during the statutory effort period at the social welfare agency, a run-in period has been created: only participants who return at the end of the effort period will be included in the analyses for the examination of the effectiveness of DNK.

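### The starters-only analysis is said to measure the effectiveness of actual treatment, but randomisation does not protect that comparison and the article states no assumption that would

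*Protocol article*

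**What the plan says.** The Statistical analysis section of the protocol article makes ITT the primary approach. It then adds a second analysis in which "only participants who actually started with the intervention are included". The stated reason is that by doing both, "we will be able to measure both the effectiveness of *assigned* treatment and *actual* treatment". No assumption or caveat accompanies that sentence.

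Continuous outcomes "will be analyzed with independent samples *t* tests, using treatment condition (DNK versus CAU) as independent variable". School/work gets a chi-square test and registered recidivism a Cox regression. Cohen's d is to be based on adjusted means, but no adjustment is named. The section does not say which of these methods apply to the starters-only set.

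On timing, the Design section says: "After T0, the random assignment (with a ratio between DNK and CAU of 1:1) will be carried out by the first author". The young adult learns his condition from the youth coach at the second interview, and no intervention takes place before then. Under Control condition, the youth coach decides which programme a CAU participant is referred to. Under Experimental condition, DNK is a single programme, usually four days a week in its first two phases.

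The Discussion comments: "Another possible threat to the value of our study is the risk of nonadherence to interventions". It attributes that risk to the participants' multiple problems, the difficult referral path and the early randomisation.

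**The concern.** Limiting both arms to starters conditions on something that happens after randomisation. Randomisation makes the arms comparable as allocated. It does not make the starters in one arm comparable with the starters in the other. Here the participant knows what he has been offered when he starts or fails to start, what he would start differs between the arms, and the Discussion links nonadherence to the severity of participants' problems. Each of these gives a reason why the two groups of starters could differ in prognosis.

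What is at stake is interpretation. The Discussion says that the trial is meant to inform referrers, policy-makers and politicians. If ITT showed little difference and the starters-only contrast showed a benefit, the current sentence would allow the second result to be read as the effect of receiving DNK. The design does not support that reading on its own.

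**Working it through.** **The plan's own figures.** The Power analysis section gives about 100 per arm, alpha .05, power .80 and a small to medium effect. Assuming a two-sided test and d = 0.40, n = 2(1.96 + 0.842)²/0.40² = 98.1, so 99 per arm, which fits. The article gives no numerical d: d = 0.30 would need 175 per arm and d = 0.50 would need 63. Allowing for 34% dropout, 100/(1 − 0.34) = 152, against 150 stated. Allowing for 40% run-in loss, 300/(1 − 0.40) = 500, as stated. These figures are not in dispute. They supply only a yardstick of d ≈ 0.40.

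**Order of events**, from Design, Control condition and Discussion:
1. T0, then randomisation.
2. The effort period, with no intervention. Non-returners are excluded from the analyses.
3. Second interview: the participant is told his condition.
4. Referral: DNK in one arm, a programme chosen by the coach in the other.
5. Start or no start. Only those who start enter the second analysis.

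The analysis set is thus fixed at step 5, after allocation is known and after the arms have diverged.

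**Illustration of size.** The article gives no start rates and no strength of selection, so both are assumed. Suppose treatment has no effect, the outcome is standardised, and a participant starts when a normally distributed propensity exceeds a cut-off. Let ρ be the correlation of that propensity with outcome, p the proportion starting and z the cut-off. The mean outcome among starters is then ρ·φ(z)/p, and the spurious difference is

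bias = ρ × [φ(z₁)/p₁ − φ(z₂)/p₂].

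- φ(z)/p is 0.644 at p = 60% and 0.350 at p = 80%, a difference of 0.294.
- ρ = 0.2: 0.2 × 0.294 = 0.06.
- ρ = 0.5: 0.5 × 0.294 = 0.15.

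Relative to d = 0.40 this is 0.06/0.40 = 15% to 0.15/0.40 = 38%.

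A simulation of 10,000 trials per scenario, with 150 per arm, no true effect and t tests at 5%, shows what drives the result:

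| Start rates, arm 1 / arm 2 | ρ, arm 1 / arm 2 | Bias (d) | Rejection, starters only | Rejection, all randomised |
|---|---|---|---|---|
| 66% / 66% | 0.35 / 0.35 | 0.00 | 4.8% | 5.1% |
| 60% / 80% | 0.35 / 0.35 | 0.10 | 12% | 5.2% |
| 66% / 66% | 0.35 / 0 | 0.19 | 29% | 5.1% |

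The first row shows that the contrast can be unbiased, when selection is alike in both arms. The third shows that equal start rates alone do not secure this. The all-randomised comparison keeps its nominal level throughout.

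**The case against.** The strongest reply is that the analysis is already subordinate. ITT is primary, the starters-only analysis is an addition, and nothing in the article makes a conclusion depend on it. That stands, and it limits the point to the interpretation of a supportive result.

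A second reply is that the run-in removes much of the problem. The expected 40% loss occurs before participants are told their arm, so many of the least engaged may leave both arms alike. This is fair as a reason to expect weaker selection afterwards. It does not address selection after disclosure, which is the selection that defines this analysis set.

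A reader might also infer more than the text supports:
- **That the analysis cannot estimate an effect of actual treatment.** This is too strong. It could if starting selected alike in both arms. The difficulty is that the article does not state or support this condition.
- **That the groups are purely self-selected.** In CAU the coach's referral also shapes who starts what.
- **That the bias would favour DNK because it is more demanding.** The direction is unknown. DNK also offers free meals, on-site psychological support and home visits for participants with very severe problems, any of which could raise uptake. The 34% in the Power analysis section is another study's dropout between pretest and posttest, not a rate of failing to start.
- **That only unadjusted t tests and chi-square tests are planned.** Cox regression and adjusted means are mentioned too, and the article refers to a fuller ethics-committee protocol for detail on methods. Missing detail on covariates is therefore not the complaint. The complaint is a claim that the article itself makes.

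**Conclusion.** The point holds as one about an overstated claim for a secondary analysis. The starters-only comparison gives up the protection of randomisation, and the article credits it with measuring actual-treatment effectiveness without naming the condition that this requires. The primary ITT comparison is unaffected by this point.

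The size and direction of bias cannot be derived from the article. The d of about 0.06 to 0.15 rests on assumed start rates of 60% and 80%, the same selection correlation of 0.2 to 0.5 in both arms, normality and no true effect. It shows that a bias which matters beside d ≈ 0.40 is plausible, not that it will occur.

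**What to change.** In Statistical analysis, delete the claim that this analysis measures the effectiveness of actual treatment. Describe it as a supportive, non-randomised comparison of starters that is open to selection bias. Report the start rate in each arm and the T0 characteristics of starters and non-starters by arm. State that conclusions on effectiveness rest on the ITT analysis.

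Adjustment or weighting on T0 variables is optional. If used, it should be reported with its assumption of no unmeasured confounding. That assumption is doubtful here: Table 1 schedules the motivation questionnaire only at T1 and T2, and its footnote limits it to respondents who are in a programme or have just finished one. Baseline motivation is therefore not measured, and non-starters have no score. A complier-average estimate is another option, with its own assumptions to state. Choosing between the two is a trade-off, and the correction does not depend on it.

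The cost is a few sentences and a descriptive table from data already planned, since the Discussion says that participants who drop out before intervention are also followed up. The downside is a less favourable label for a secondary result.

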### Power analysis

Power calculations (conducted with G* power) indicate that approximately 100 multi-problem young adults per treatment condition (assuming an alpha of .05, a power of .80, and a small to medium effect size) are sufficient to detect a difference in treatment effects at T3. However, we expect some dropout after referral to the interventions. James and colleagues [78], for example, had to deal with a dropout rate of approximately 34% (p. 1163) between pre and posttest (i.e., 9 months after baseline) in a group of juvenile and young adult offenders. Therefore, we aim to include 150 participants per treatment condition. To include 300 multi-problem young adults in total in our study, we need to recruit 500 participants at the social welfare agency as the estimated dropout rate here within the effort period is 40% (p. 9) [71].

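### Missing T3 data are said to be multiply imputed but the method is described as EM maximum likelihood; a t test on one EM-completed data set would have a type I error well above 5%

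*Protocol article*

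**What the plan says.** All of this stands in the protocol article.

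- **Main comparison** (Statistical analysis): "The outcomes at T3 will be used to determine the main effects of DNK compared to CAU".
- **Missing data** (same section): "Missing data at T3 will be imputed according to the multiple imputation approach, for which we will use LISREL 8.8". The next sentence describes the method: "This approach follows the expectation maximization algorithm (maximum likelihood estimation"), with two references.
- **Test** (same section): independent-samples t tests for the continuous outcomes, "using treatment condition (DNK versus CAU) as independent variable and the outcome measures as dependent variables". Self-reported recidivism and self-sufficiency are among them, and both belong to the primary outcomes. Cohen's d is to be "based on adjusted means and standard deviations".
- **Registered recidivism** (same section): survival curves and Cox regression on recorded offences.
- **Additional analyses** (same section): mixed models for the continuous outcomes on T0, T2 and T3. The text does not say that these use imputed data.
- **Expected loss** (Power analysis): about 100 per arm, "assuming an alpha of .05, a power of .80, and a small to medium effect size". This is raised to 150 per arm because a cited study "had to deal with a dropout rate of approximately 34" per cent by about 9 months after baseline.

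**The concern.** EM and multiple imputation are different procedures. EM converges on one set of maximum-likelihood estimates, from which each missing score can be replaced by one value. Multiple imputation draws parameters and values several times, analyses each completed data set, and adds the variance between the results to the variance within them. The article equates the two and then goes straight to a t test. An analyst who follows the sentence literally produces one completed file and tests it as if all 300 scores had been observed.

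This is a statement about the method, not mere silence on detail, and it concerns the comparison that the article calls the main one. If it were carried out that way, the p values and confidence intervals for self-sufficiency and self-reported recidivism would overstate the evidence in either direction.

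**Working it through.** **The plan's own allowance.** 100 / (1 − 0.34) = 151.5, so 152 per arm against the stated 150. In reverse, 150 × 0.66 = 99 observed per arm. The 34% is therefore the allowance behind the target.

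**Inputs.** From the article: n = 150 per arm, m = 0.34 missing, alpha 0.05 (taken as two-sided, since the article does not say). Assumed, because the article gives neither: T3 scores missing completely at random, and a T0–T3 correlation r of 0.3, 0.5 or 0.7. The outcome SD is set to 1. The imputation uses arm and T0.

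**Case A: each missing score replaced by its EM conditional mean.**

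- The completed scores lose the residual variance of the missing part, so the t test reports SE = √[(2/n)(1 − m(1 − r²))].
- The true sampling SD of the difference is √[(2/n)(r² + (1 − r²)/(1 − m))].
- At r = 0.5, the reported SE is √[(2/150)(1 − 0.34 × 0.75)] = √(0.01333 × 0.745) = 0.0997.
- At r = 0.5, the true SD is √[(2/150)(0.25 + 0.75/0.66)] = √(0.01333 × 1.386) = 0.136.
- The ratio is 0.733. The critical value 1.968 (298 df) then acts as 1.968 × 0.733 = 1.44, and the two-sided type I error is about 0.15.

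**Case B: one random draw at the maximum-likelihood estimates.** The reported SE is √(2/150) = 0.1155. The term m(1 − r²) is added to the bracket for the true variance. At r = 0.5 the true SD is √[0.01333 × (1.386 + 0.255)] = 0.148, the ratio is 0.78 and the type I error is about 0.12.

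**Simulation.** 4,000 null trials per setting, with the same inputs:

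| Missing | r | A: formula | A: simulated | B: simulated | Proper MI, 20 draws, Rubin's rules |
|---|---|---|---|---|---|
| 34% | 0.3 | 0.177 | 0.172 | 0.140 | 0.052 |
| 34% | 0.5 | 0.149 | 0.153 | 0.128 | 0.051 |
| 34% | 0.7 | 0.111 | 0.107 | 0.102 | 0.051 |
| 20% | 0.5 | 0.096 | 0.087 | 0.082 | 0.045 |
| 10% | 0.5 | 0.069 | 0.061 | 0.061 | 0.046 |

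A separate simulation at 34% missing gave 0.19 / 0.16 / 0.11 for case A and 0.15 / 0.12 / 0.11 for case B at r = 0.3 / 0.5 / 0.7. Another gave 0.098 and 0.067 for case A at 20% and 10% missing. With proper multiple imputation at 34% missing, the mean SE was 0.99 to 1.01 times the true SD.

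**Effect size.** In case A the SD of the completed scores shrinks by √(1 − m(1 − r²)). A Cohen's d built on it is inflated by 1/√0.691 = 1.20 at r = 0.3 and 1/√0.827 = 1.10 at r = 0.7.

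**The case against.** The strongest reply is that the article does name multiple imputation and nowhere says that one completed data set is made, that conditional means are filled in, or that results go unpooled. EM can be a legitimate step in a proper procedure, for example to start the draws. The two references cannot be checked here, and the article refers to its ethics-committee protocol for a more detailed description of methods. The number of imputations, the pooling rule and the predictors are normally left to such a document. This stands, and it makes the size conditional. It does not rescue the sentence, which identifies the method with an algorithm that is not multiple imputation.

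The size is also open to challenge. The 34% is another study's loss at about 9 months, while T3 is at 14 months and the Discussion plans intensive tracing. A better predictor helps too: if T2 were known for everyone and correlated 0.8 with T3, case A gives a ratio of √(0.8776/1.1855) = 0.86 and a type I error of about 0.09. The inflation shrinks but does not vanish.

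Two stronger readings are tempting and not supported:

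- A reader might infer that T1 scores are barred from the imputation, from "T1 data are excluded from the analyses since T1 is an additional assessment point to measure treatment characteristics". That sentence belongs to the mixed-model and GEE analyses. The imputation text excludes no predictor.
- A reader might infer that allocation is left out of the imputation model, which would pull the effect towards zero. The article does not say what the model contains, and silence there is no evidence of omission.

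**Conclusion.** The description is wrong as written and should be corrected. That the standard errors will in fact be too small is not established, because a single unpooled data set is the literal reading and not a stated fact.

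On that reading, with 34% missing, the nominal 5% t test has a type I error of roughly 10 to 19%, about two to four times the stated rate. At r = 0.5 it is about 9 to 10% with 20% missing and 6 to 7% with 10% missing. These figures rest on 150 per arm, values missing completely at random, and T0–T3 correlations that the article does not give.

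The point concerns the T3 t tests of the continuous outcomes, two of which bear on the primary outcomes. It does not reach the Cox analysis of registered recidivism, and the mixed models are not described as using imputed data.

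**What to change.** Replace the EM sentence by one of the following before outcomes are analysed. Trial status says that data collection runs until January 2018 and effects are unknown until then.

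1. **Proper multiple imputation.** State that several data sets are drawn with parameter uncertainty, with allocation and the earlier outcome scores in the imputation model. Each set is analysed with the planned test, and the results are pooled by Rubin's rules. If EM only starts the draws, say so.
2. **The planned mixed model.** Take the DNK–CAU contrast at T3 from the mixed model already specified, fitted to unimputed data, as the main estimate for the continuous outcomes.

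Either costs a change of wording and perhaps of software routine. The downside is wider confidence intervals than a single completed data set would show: at r = 0.5 and 34% missing, the mean SE in the simulation was 0.137 with proper imputation against 0.100 in case A. The wider interval is the correct one.
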